### **6.1. Primary Efficacy Endpoint**

- 1) Change from baseline in the Severe Impairment Battery (SIB) score at Visit 15 (Week 24).

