#### 7.5. Maintenance of Blinding and Unblinding

To maintain double blind, in this clinical trial, the investigational product and the investigational reference product (placebo) will be packed so that no differences in the appearance are visibly observed between the two.

At the time when all patients have completed the trial, the unblinding can be done by performing the Database Locking. However, the information of the administration group, in case of unblinding, can be confirmed only by the sponsor and the CRO which conducts statistical analysis.

If the patient is required to be unblinded (the code is required to be opened) inevitably due to the occurrence of a serious ADR during the clinical trial; or this is deemed necessary by GemVax & KAEL Co., Ltd. for the patient's right and interest, and safety, only the unique code of the patient is allowed to be opened through the IWRS. In case unblinding is required, it can be made only for the patient by the investigator after consultation with the sponsor. The reason for unblinding and the date of unblinding should be documented and kept. The patient whose randomization code is unlocked cannot continue to participate in this clinical trial.

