### **7.6.2. Prohibited concomitant medications and therapy**

The following concomitant medications are prohibited from screening (visit 1) to end-of-study visit.

Prohibited items are not limited to the concomitant medications and combination therapies specified below, and any medications judged by the investigator to have an effect on evaluating the efficacy of this clinical trial can also be prohibited.

If the prohibited concomitant medications need to be used for the treatment of patients over the duration of this clinical trial according to the judgment of investigators or doctors in charge

of other medical symptoms, the patients should immediately discontinue this clinical trial and this will have to be recorded in detail in the CRF.

- ① Other drugs for AD other than donepezil : Acetylcholinesterase inhibitors (rivastigmine, galantamine, etc.), NMDA receptor antagonists (memantine, etc.)
- ② Choline excitatory drugs (However, drugs for local administration such as choline agonists and pilocarpine collyrium are allowed.)
- ③ CNS stimulants (Methylphenidate, Modafinil, Pemoline, Atomoxetine)
- ④ Antidepressant drugs (tricyclic antidepressants, MAO inhibitors)
- ⑤ Typical antipsychotic drugs (Bromperidol, Chlorpromazine, Haloperidol)
- ⑥ Anticholinergic drugs (Atropine, Glycopyrrolate, Scopolamine, Homatropine, Ipratropium)  
However, the short-term use for the purpose of alleviating the symptoms of digestive system is allowed.)
- ⑦ All investigational products or medical devices not specified in this trial.
- ⑧ Use of any abused drug (including but not limited to illegal amphetamines, hemp, cocaine, illegal opiate drugs, propoxyphene, methadone, methaqualone, phencyclidine or illegal barbiturates)
- ⑨ Previous administration of all investigational vaccines for AD
- ⑩ Regular use of narcotics (for 3 days or more a week)
- ⑪ Other drugs affecting the immune system

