#### **12.1.1.1. SIB (Severe Impairment Battery)**

SIB evaluation will be conducted at Visits 2, 9 and 15.

The SIB (Saxton et al., 1990) was developed to evaluate dementia patients with severe cognitive impairment and consists of easy and simple questions. The questionnaire consists of 50 questions for the 9 items of "orientation", "social interaction", "construction", "orienting to name", "language", "memory", "praxis", "visuo-spatial ability". The scores range from 0 to 100 points, and the better the state of the patient, the higher the score.

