**12.2.7. Visit 15 (24 weeks  $\pm$  3 days ; Administration of the Investigational Product)**

This visit will be conducted at 24 weeks after Visit 1, and evaluations to be made at this visit are as follows. Even the patients who drop out of this clinical trial should undergo the tests conducted at Visit 15.

- 1) Any change in concomitant medication will be checked in comparison to last visit.
- 2) Physical examination will be carried out.
- 3) Vital signs (blood pressure, pulse rate, respiration, and body temperature), height, and body weight will be measured.
- 4) Laboratory tests will be conducted.
- 5) SIB test will be conducted.
- 6) K-MMSE test will be conducted.
- 7) CDR-SOB test will be conducted.
- 8) CIBIC-Plus test will be conducted.
- 9) NPI test will be conducted.
- 10) GDS test will be conducted.
- 11) ADCS-ADL-severe test will be conducted.
- 12) Incidence of AEs and the details will be investigated.
- 13) The investigational product will be administered (Whether there is any AE will be observed for 30 minutes after the administration).
- 14) For female patients of childbearing age, pregnancy test will be conducted.
- 15) The next visit date (Visit 16) will be set.

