#### 14. CRITERIA OF TRIAL DISCONTINUATION AND DROPOUTS

##### 14.1. Criteria of Trial Discontinuation and Dropouts

Patients are free to withdraw from this clinical trial at their request at any time. The investigator or sponsor is also free to withdraw a patient at any time for the reasons of safety, action, and administration.

The investigator should inquire of the patient about a cause of dropout in this trial and ask him/her to make the last visit so that all tests can be performed as scheduled at Visit 15. If the patient does not make the scheduled visit, the investigator should make every effort to contact him/her and document results of tests related to the patient as best he/she can. The investigator should also do his/her best to identify the reason why the patient dropped out of this trial, ask for the return of unused investigational products, and continue to monitor the patient (follow-up) with regard to unresolved adverse events.

In case the patient withdraws his/her consent, further evaluation and additional data collection will no longer be possible, even if agreement to the personal information disclosure is withdrawn. All data collected prior to the withdrawal of consent can be continuously kept and used by the sponsor.

The following are the cases where the patient can stop and drop out of this clinical trial over the duration of clinical trial.

- ① In case the patient or the patient's legally authorized representative agrees to withdraw the consent to participation in this clinical trial
- ② In case the patient is found to have violated the inclusion/exclusion criteria
- ③ In case the patient is found to have violated the important study plan specified in the clinical trial protocol
- ④ In case the continuous administration and observations are not appropriate for this trial due to AE or SAE according to the investigator's judgment
- ⑤ In case the investigator has difficulty in administering the investigational product to the patient
- ⑥ In case the investigator judges that follow-up of the patient is impossible
- ⑦ In case the patient took the prohibited concomitant medication; or in case the investigator judges that the patient needs treatment with the prohibited concomitant medication
- ⑧ In case the investigator decides that it is not appropriate for the patient to continue to participate in this trial

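### The protocol makes no clear provision to collect the Week-24 SIB from patients who stop the product without withdrawing consent, and exit scores can share the Visit 15 label

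*Protocol*

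**What the plan says.** The primary endpoint is the change in SIB from baseline to Visit 15, Week 24 (Protocol 6.1). SIB is measured three times: "SIB evaluation will be conducted at Visits 2, 9 and 15" (12.1.1.1).

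Two rules make leaving the trial mandatory:
- **Prohibited medication (7.6.2).** If such a drug is needed, "the patients should immediately discontinue this clinical trial and this will have to be recorded in detail in the CRF". The list covers other AD drugs (cholinesterase inhibitors other than donepezil, memantine), typical antipsychotics and some antidepressants.
- **Code break (7.5).** "The patient whose randomization code is unlocked cannot continue to participate in this clinical trial".

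Section 14.1 then lists cases in which a patient may drop out. They include adverse events, difficulty in giving the product, and the case where "the investigator judges that the patient needs treatment with the prohibited concomitant medication".

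For leavers, 14.1 tells the investigator to "ask him/her to make the last visit so that all tests can be performed as scheduled at Visit 15". Section 12.2.7, headed as the 24-week visit, adds: "Even the patients who drop out of this clinical trial should undergo the tests conducted at Visit 15". After that visit, 14.1 mentions continued follow-up only for unresolved adverse events. It rules out further data collection when consent is withdrawn and states no such bar for other leavers. Section 15.1.6 carries the last observation forward in the FAS.

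**The concern.** In 7.5 and 7.6.2 the rule ends participation, not dosing alone. A patient who leaves at, say, Week 8 and has the final tests then will have a Week-8 SIB, possibly recorded as Visit 15, and nothing at Week 24. No section clearly asks a patient who stops the product but still consents to come back for SIB at Week 12 or Week 24.

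Section 9.3 gives the aim as evaluating whether GV1001 reduces disease progression. Worsening AD can prompt the addition of another AD drug or a typical antipsychotic, so leaving can depend on the outcome being measured. Visit attendance is fixed by the protocol, and no later analysis plan can recover a score that was not taken.

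**Working it through.** **1. When are a leaver's Visit 15 tests done?**

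| Text | Points to |
|---|---|
| 14.1: the visit is the patient's last, described alongside asking the cause of dropout and asking for unused product back | Exit |
| 14.1: later follow-up named only for unresolved adverse events | Exit |
| 15.1.6: for a patient who drops out early, the latest value stands in for the missing time point | Exit (presupposes no real Week-24 value) |
| 14.1: tests as scheduled for Visit 15, with efforts to make contact if the scheduled visit is missed | Week 24 possible |
| 12.2.7: the dropout sentence sits under the heading of 24 weeks ± 3 days | Week 24 possible |

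Exit is the more natural reading, but it is not stated outright. Sites could apply both readings and file both kinds of score under Visit 15.

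**2. How many patients?**

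Inputs from 9.3: 24 evaluable per group, 20% dropout.
- Planned size: 24 / (1 − 0.20) = 30 per group; 3 × 30 = 90. This reproduces the protocol's figures.
- Planned leavers: 30 − 24 = 6 per arm; 90 − 72 = 18 in total.

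The 20% is all-cause. It includes consent withdrawals and patients who cannot be followed, whom no rule on visits can recover. The protocol does not say how many leave because of worsening.

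**3. What an exit score can do to the result**

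The protocol gives no expected SIB decline, so this is an illustration. Assume a linear decline of D points over 24 weeks and exit at Week t, with the exit score standing in for Week 24.
- Decline missed per leaver = D × (1 − t/24).
- Shift in an arm mean = dropout share × D × (1 − t/24).

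| D (assumed) | Exit week (assumed) | Missed per leaver | Arm-mean shift at 20% dropout |
|---|---|---|---|
| 4 | 18 | 4 × 0.25 = 1.0 | 0.20 × 1.0 = 0.2 |
| 10 | 12 | 10 × 0.50 = 5.0 | 0.20 × 5.0 = 1.0 |
| 15 | 6 | 15 × 0.75 = 11.25 | 0.20 × 11.25 = 2.25 |

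Over D = 4 to 15 and exit at Weeks 6 to 18, an arm mean looks 0.2 to 2.25 SIB points better than it is. With equal dropout, timing and decline in the arms, the shift cancels in the treatment difference. With 30% dropout in one arm and 10% in another, the multiplier is 0.30 − 0.10 = 0.20, so the same 0.2 to 2.25 points become a bias in favour of the arm with more leavers.

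**The case against.** The strongest case on the other side has five parts.

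- **Week-24 data may be collected.** A reader might infer that Week-24 scores are never obtained from leavers. The documents do not support that: the wording in 14.1 and the heading of 12.2.7 allow a Week-24 visit. What stands is an unclear time point, with exit the likelier reading.
- **Stopping treatment is not always leaving the trial.** A reader might infer that it is. Section 16.5 keeps follow-up after treatment ends for pregnancy, section 13 stops only administration for immune-related events, and the list in 14.1 is permissive. Only 7.5 and 7.6.2 are mandatory. The objection stands to that extent, though none of these sections asks for a Week-24 SIB. Pregnancy also has little weight at ages 55 to 85.
- **The protocol already separates consent withdrawal from other exits.** It does, in 14.1. This means that other leavers could be observed, but the text does not use the distinction to request efficacy visits.
- **The route through deterioration is narrow.** Section 7.6.3 permits atypical antipsychotics, SSRIs, anxiolytics, sleeping pills and anticonvulsants, so many drugs for behavioural worsening do not force an exit. This stands. The route through other AD drugs and typical antipsychotics remains.
- **Later scores may answer another question.** Scores after a new AD drug no longer reflect the add-on-to-donepezil comparison alone, and after a code break interview-based ratings such as CDR-SOB may be unblinded. In a trial that 11.1 calls a pilot, the choice of question is partly a preference. This argues for flagging such scores; it does not argue for leaving them uncollected.

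**Conclusion.** The point holds as an unclear provision with a real data-collection gap behind it. Sections 7.5 and 7.6.2 take certain patients out of the trial, 14.1 gives leavers one last visit, and no section clearly asks those who still consent for SIB at calendar Week 24. Exit and Week-24 scores can share a label.

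At the planned dropout the gap reaches at most 18 of 90 patients, 6 per arm. It would be tempting to apply a return rate to all 18 (at 50–70%, 9 to 13 values), but the protocol gives no basis for such a rate, and the 18 include patients who cannot be recovered. The shift of 0.2 to 2.25 points in an arm mean rests on assumed decline and exit times. It biases the comparison only if dropout, its timing or the decline differs between arms. Correcting the text is worthwhile because it is cheap and concerns the primary endpoint.

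**What to change.** Leave the list of prohibited drugs and the rules on when treatment stops unchanged, and change the data-collection text:

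1. In 12.2.7 and 14.1, with cross-references in 7.5 and 7.6.2, state that a patient who stops the product but has not withdrawn consent is asked to attend the efficacy visits still ahead (Visits 9 and 15) on their planned dates, with any new AD drug recorded.
2. Record tests done at the time of stopping under a separate early-termination label, not as Visit 15.
3. Flag Week-24 scores taken off treatment, on another AD drug or after a code break, so that the analysis can treat them explicitly.
4. Reconcile the mandatory exit for prohibited medication in 7.6.2 with the permissive list in 14.1, which names the same case.

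The cost is protocol wording, at most two already scheduled visits per such patient (no more than about 18 patients at the planned dropout), and a set of flagged values that the analysis must handle. The sample size does not change.

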### 7.6.3. Drugs requiring caution

The following drugs can be taken over the duration of this clinical trial, but careful administration is required. The drug name, administration & dosage, and administration period should be recorded in the CRF.

- ① Anticholinergic drugs (antispasmodics, asthma drugs, etc. which represent anticholinergic effect except prohibited medications)
- ② Sleeping pills (fast-acting sleeping pills ; drugs known to affect the central nervous system such as zolpidem, brotizolam, lormetazepam, rilmafazone, zopiclone, ramelteon), anticonvulsants, atypical antipsychotics (seroquel, cacepin, etc.), anxiolytics, antidepressants (tricyclic antidepressants, antidepressants other than MAO inhibitors, SSRIs, etc.)
- ③ In case of drugs that can affect the efficacy evaluation of the investigational product such as Vitamin E, Ginko biloba extracts, estrogens, and brain function improvers (citicoline, oxiracetam, piracetam, acetyl-L-carnitine, Nimodipine, etc.), the administration of them is acceptable without changes in dosage and administration over the duration of this clinical

trial as long as they are administered at intermittent, low doses for a short period of time ( $\leq 2$  months in a row) and at stable doses from 2 weeks prior to the administration of the investigational product. However, the cognitive function should be evaluated 3 hours after the time when a drug that affects the efficacy evaluation of the investigational product is taken.

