#### **15.1.7. Handling of protocol violations**

The principal investigator and the subinvestigator should be well-acquainted with the protocol and thoroughly carry out the clinical trial procedures as specified in the protocol so that any protocol violation does not occur. In order to comply with the schedules for the administration of the investigational product and tests in this clinical trial, the investigator should take appropriate measures, such as written notification or telephone monitoring related to visit time, so that the patient can attend the visit on the date. On the other hand, the inevitable protocol violation should be handled as follows:

In case of a serious violation of the clinical trial protocol, the patient should be eliminated from the analysis (excluding PPS). Refer to the items below:

- ① In case the patient has no signed consent form.
- ② In case the patient is found to have violated the inclusion/exclusion criteria
- ③ In case the patient took the prohibited concomitant medication over the duration of clinical trial
- ④ In case the primary efficacy evaluation tests at the time of the initiation-termination of this trial were missing.

When it comes to minor protocol violations, which are judged to have no effect on the interpretation of the clinical trial results, the degrees and causes of violations or delays should be exactly recorded. Whether this affected this clinical trial will be comprehensively considered through the blind meeting prior to Database Lock, and will be included in the PPS analysis.

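### Tricyclic antidepressants are prohibited in Section 7.6.2 and exclusion criterion 12 but permitted with caution in Section 7.6.3, so withdrawal and per-protocol membership depend on which section is read

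*Protocol*

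**What the plan says.** Protocol Section 7.6.2 opens with "The following concomitant medications are prohibited from screening (visit 1) to end-of-study visit". Item 4 of its list is "Antidepressant drugs (tricyclic antidepressants, MAO inhibitors". If a patient comes to need one of the listed drugs, "the patients should immediately discontinue this clinical trial and this will have to be recorded in detail in the CRF". Exclusion criterion 12, in the synopsis and in Section 9.2, refers to Section 7.6.2 and again names tricyclics.

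Section 7.6.3 has the opposite introduction: "The following drugs can be taken over the duration of this clinical trial, but careful administration is required". It asks only that the drug, its dosage and its period of use be entered in the CRF. Item 2 of that list contains "antidepressants (tricyclic antidepressants, antidepressants other than MAO inhibitors, SSRIs, etc".

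Two later sections attach consequences to prohibited drugs. Item 7 of the dropout criteria in Section 14.1 begins "In case the patient took the prohibited concomitant medication; or in case the investigator judges". Item 3 of the serious violations in Section 15.1.7 is "In case the patient took the prohibited concomitant medication over the duration of clinical trial".

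**The concern.** The prohibited list governs who may enter, who must stop and who counts as per protocol. If one drug class appears by name on both the prohibited list and the permitted list, two sites can handle identical patients in opposite ways, and each can cite the protocol.

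Two things are at stake. The first is the primary endpoint. A patient stopped because of a tricyclic has no true Week 24 SIB value, although under the other section that patient would have continued to Visit 15. The second is the per-protocol set, whose membership for tricyclic users would depend on which section the person classifying deviations had in mind. Section 7.6.3 itself places antidepressants beside sleeping pills and other drugs acting on the central nervous system, and depression is one of the NPI domains in Section 12.1.1.5. The class is therefore not incidental to the efficacy scales.

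**Working it through.** No arithmetic applies, because the protocol states no figure that bears on the point. The check is a comparison of texts.

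1. **Same class, opposite status.** Section 7.6.2 item 4 and exclusion 12 (both places) prohibit tricyclics by name. Section 7.6.3 item 2 permits them by name. Its next phrase, antidepressants other than MAO inhibitors, would also take them in.

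2. **Is there a clause that settles it?** Item 1 of Section 7.6.3, on anticholinergics, limits itself to drugs "which represent anticholinergic effect except prohibited medications". The antidepressant entry in item 2 has no such limit, and its only carve-out is for MAO inhibitors. Nothing in Section 7.6.3 gives Section 7.6.2 precedence.

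3. **What follows from each reading:**

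| | Read under 7.6.2 | Read under 7.6.3 |
|---|---|---|
| Tricyclic user at screening | Excluded by criterion 12 | Use permitted |
| Tricyclic needed during the trial | Immediate discontinuation | Continue, record in CRF |
| Section 14.1 | Listed ground for dropout | Not triggered |
| Section 15.1.7 | Listed serious violation | Not triggered |
| Per-protocol set (Section 15.1.1) | Out, since it requires completion without violation | In, if nothing else intervenes |

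4. **Effect in the full analysis set.** Section 15.1.1 admits treated patients whose primary efficacy data can be obtained and excludes nobody for medication. Section 15.1.2 makes this the main efficacy set. SIB is measured only at Visits 2, 9 and 15 (Section 12.1.1.1). Sections 12.2.7 and 14.1 ask dropouts to undergo the Visit 15 tests when they leave, and Section 15.1.6 carries the last observation forward otherwise. A withdrawn user with SIB data therefore stays in the main analysis, but with an early assessment or a carried-forward score in place of a Week 24 value.

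5. **Effect in the per-protocol set.** Section 15.1.6 does not apply carrying forward there, so the effect is membership itself. The blind meeting in Section 15.1.7 is described for minor violations. Prohibited medication is listed as serious, so the meeting does not clearly resolve the conflict.

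6. **Number affected.** The protocol gives no rate of tricyclic use at entry or during the trial, so no count can be derived.

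**The case against.** The strongest reply is that Section 7.6.3 contains a slip of wording. If antidepressants other than MAO inhibitors are allowed, naming tricyclics and SSRIs separately is redundant. The rest of the section complements Section 7.6.2: item 1 sets prohibited anticholinergics aside, and item 2 lists atypical antipsychotics where Section 7.6.2 prohibits typical ones. Three places prohibit tricyclics and one permits them. This makes a slip plausible, and it means that sites might in practice treat patients alike. It remains an inference, however. Sites act on the text, and the text as written permits what other sections prohibit.

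A second reply is that few patients would be affected. Exclusion 12 covers those already taking or scheduled to receive a tricyclic, and exclusion 3 addresses a history of depression. If both are applied, only unplanned starts during the trial remain. This stands as a limit on size. Any percentage per arm would rest on an invented usage rate.

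Three stronger readings are tempting, and the documents do not support them:

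- A reader might infer from Section 15.1.7 that users are removed from all analyses. The sentence speaks of elimination from the analysis and then adds an unclear bracket about the PPS. Since the full analysis set has no medication exclusion, the most plausible meaning is removal from the per-protocol set only.
- A reader might infer that withdrawal is uniformly mandatory. Section 7.6.2 is firm, but Section 14.1 lists cases in which a patient can stop.
- A reader might see a parallel contradiction between Section 7.6.2 item 9, on previous Alzheimer vaccines, and exclusion 18, on vaccine-trial participation within 6 months. Exclusion criteria are cumulative and meeting any one suffices, so these rules overlap without conflicting.

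**Conclusion.** The contradiction is real. Tricyclic antidepressants are named as prohibited in Section 7.6.2 and in exclusion 12, and named as permitted with caution in Section 7.6.3, with no clause to decide between them. It affects eligibility, withdrawal and per-protocol membership. In the main efficacy set it acts only through avoidable early stopping and the substitute Week 24 value that follows.

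Its numerical size is unknown and may be zero. The conclusion on the per-protocol set rests on reading the unclear bracket in Section 15.1.7 as exclusion from that set. The conclusion that there is a conflict rests on the literal text alone and holds whether or not Section 7.6.3 contains a slip. The documents do not settle which status was intended, and this review does not choose one.

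**What to change.** Reconcile Section 7.6.2 item 4, Section 7.6.3 item 2 and exclusion criterion 12 (synopsis and Section 9.2) so that each antidepressant class has exactly one status. The sponsor's clinical team decides which. Issue the reconciled list to all sites, and use that one list both for withdrawal decisions and for per-protocol classification before database lock.

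The cost is a clarifying amendment and a letter to sites. No additional data are needed.
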